**Methods:**

A randomized clinical trial of elderly frail patients drawn from the Clinical Management Unit “Tiro de Pichón”, Health District of Malaga, will be included in the study (after meeting the inclusion / exclusion criteria) will be randomized in two groups: a control group that will undergo an intervention consistent of medication review + diet adjustment + health education (regular workout recommendations within a complete advice on healthy lifestyles) and an experimental group whose intervention will consist of a multimodal treatment: therapeutic workout program+ medication review+ diet adjustment + health education. The sociodemographic, clinical and tracing variables will be reflected at the beginning of the study. In addition, the follow-up variables will be gathered at the second and sixth months after the beginning of the treatment and at the third and sixth months after the treatment (follow-up). The follow-up variables that will be measured are: body mass index, general health condition, fatigue, frailty, motor control, attention- concentration- memory, motor memory, spatial orientation, grip strength, balance (static, semi-dynamic), gait speed and metabolomics.

A descriptive analysis of the sociodemographic variables of the participants will be conducted. One-Factor ANOVA will be used for the Within-Subject analysis and as for the Between-Subject analysis, the outcome variables between both the groups in each moment of the data collection will be compared.

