## Methods/design

### Hypothesis

The interaction of various intervention strategies, wherein a supervised workout program, medication review, diet adjustment and health education are included, should achieve further improvements of the neuromuscular and physiological state in the elderly identified as frail, than the standard medical practice.

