### Objective

Short-term and mid-term comparison of the efficacy of a multimodal program that incorporates a therapeutic workout program, medication review, diet adjustment and health education, in comparison to the standard medical practice in the improvement of the neuromuscular and physiological condition. Furthermore, it is intended to analyse the maintenance of these effects in a long-term follow-up (12 months) from the onset of the intervention. The workout program consists of a specific part for the development of strength followed by another specific part for endurance training. This sequence has better results than if structured inversely according to previous study [50].

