There will be three moments of data collection throughout the intervention: before the intervention, 2 months after the onset and after 6 months. Moreover, there will be a follow-up with two additional measurements: one 3 months and another one 6 months, after the conclusion of the intervention (9 and 12 months from the onset of the intervention, respectively).

The medication review will be focused on the regular, or at least every six months, review of the polypharmacy (intake of more than 5 drugs) insisting on the psychotropic medication due to its greater association to falls and the drugs that can negatively affect people with risk of falling under the STOPP/STAR criteria.

Diet adjustment includes the examination of the variety of nutrients and the protein intake as a protective factor. Anthropometric measurements, weight/height and BMI will be used.

The intervention on the potential hazards at home include conducting the home risk assessment template provided as the Annex 8 of the Consensus document on prevention of frailty and falls in the elderly, and intervening on modifiable elements, obstacles on the floor, mats, cables, lighting type at home, arrangement of the kitchen utensils, bathroom features, type of footwear, clothing and presence of pets.

Team members will reinforce the standard practice by the elements described above in order to improve the condition of frailty.

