### Statistical analysis

A descriptive analysis of the socio-demographic variables of the participants will be conducted.

In order to analyse the existent differences in the variable values of interest between the control group and the experimental group, Student’s T-Test will be applied for two independent samples in the case that the normality condition could be accepted, which will be verified by the Saphiro-Wilk test. In case if normality couldn’t be accepted, the appropriate nonparametric test of Mann-Whitey will be conducted.

To analyse the existent differences in the response variables prior to and after the intervention, Student’s T-Test will be carried out for paired samples in the case that the condition of normality could be accepted. In any other case, the appropriate nonparametric test of Wilcoxon will be conducted.

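### The protocol names two different within-subject analyses. Before-after tests cannot answer its comparative hypothesis, and the valid between-arm tests include no contrast for maintenance from 6 to 12 months.

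*Protocol article*

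**What the plan says.** The protocol article describes the within-subject analysis twice.

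- Abstract, Methods: "One-Factor ANOVA will be used for the Within-Subject analysis".
- Statistical analysis: "To analyse the existent differences in the response variables prior to and after the intervention", the method is as follows: "Student’s T-Test will be carried out for paired samples in the case that the condition of normality could be accepted". The Wilcoxon test is the fallback. ANOVA does not appear in this section.

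It also plans a comparison between arms.

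- Statistical analysis, for control against experimental: "Student’s T-Test will be applied for two independent samples in the case that the normality condition could be accepted", with Mann-Whitney as the fallback.
- Abstract, Methods: "the outcome variables between both the groups in each moment of the data collection will be compared".

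These analyses serve two stated aims. Under Hypothesis, the program "should achieve further improvements of the neuromuscular and physiological state in the elderly identified as frail, than the standard medical practice". Under Objective, "it is intended to analyse the maintenance of these effects in a long-term follow-up (12 months) from the onset of the intervention".

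The Experimental group section sets measurements "before the intervention, 2 months after the onset and after 6 months", and two more at 9 and 12 months from onset. That makes five visits: 0, 2, 6, 9 and 12 months.

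**The concern.** There are three linked problems.

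1. **Two methods for one question.** An ANOVA with visit as its factor is an omnibus test over the visits it includes. A paired t-test compares two occasions. In a five-visit trial the two can give different answers, and leaving both in the plan leaves the choice open until the data are seen.

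2. **A before-after test does not address the hypothesis.** Participants are screened for frailty, so some regression to the mean is likely. The cognitive and motor tests are repeated, so practice effects are likely. The control arm also receives a training schedule, a medication review and a diet plan. Both arms may therefore improve without any added effect of the program. The Statistical analysis section sets the paired test beside the between-arm test and does not say which one decides. If a reader takes significance in one arm only as evidence of benefit, the error can be large.

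3. **Maintenance has no contrast of its own.** Comparing the arms at month 12 shows whether they differ then. It does not show how much of a month-6 difference has been kept or lost.

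**Working it through.** **Side by side.**

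| Question | Abstract | Statistical analysis |
|---|---|---|
| Within-subject change | One-Factor ANOVA; visits not listed | Paired t-test or Wilcoxon, before against after; the later visit is not identified |
| Arms compared | At each data-collection time | Independent t-test or Mann-Whitney; times not listed |
| Change compared between arms, or group-by-visit | Not named | Not named |
| Baseline value used in the between-arm test | Not named | Not named |
| 6-to-12-month contrast between arms | Not named | Not named |

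**Sample size used for the check.** The Sample size section gives 100 per arm after allowing for 15% losses, so completers are 100 × (1 − 0.15) = 85 per arm. The figure of 100 cannot be reproduced, because the article gives no difference, SD or event rates. Read as a comparison of two means at 80% power and two-sided 5%, 85 per arm corresponds to a standardised difference of (1.960 + 0.842) × √(2/85) = 0.43. That is a back-calculation, not a figure from the plan.

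**How often within-arm tests mislead.** Assume an equal true change in both arms, expressed as dz, the change divided by the SD of change. The plan gives no value, so a range is shown. The power p of a paired t-test with 85 people comes from the noncentral t distribution with 84 degrees of freedom and noncentrality dz × √85. The arms are independent, so P(experimental significant, control not) = p(1 − p).

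| dz | p | p(1 − p) |
|---|---|---|
| 0.10 | 0.149 | 0.149 × 0.851 = 0.13 |
| 0.15 | 0.277 | 0.277 × 0.723 = 0.20 |
| 0.20 | 0.446 | 0.446 × 0.554 = 0.25 |
| 0.25 | 0.625 | 0.625 × 0.375 = 0.23 |

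The product cannot exceed 25%, which it reaches when p = 0.5. It falls away on both sides.

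**Simulation.** There were 10,000 runs with 85 per arm and equal change in both arms, expressed in SDs of the outcome.

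- At a pre-post correlation of 0.5 the misleading pattern appeared in 4.7%, 12.7%, 24.2%, 17.5% and 4.3% of runs for changes of 0, 0.1, 0.2, 0.3 and 0.4.
- At a correlation of 0.7 the highest rate was 22.6%, for a change of 0.2.
- In the same runs the between-arm t-test on follow-up values rejected in 4.7% to 5.2%, which is its nominal level.

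**What baseline adjustment is worth.** For the assumed difference of 0.43, a comparison of follow-up values alone needs 2 × (1.960 + 0.842)² / 0.43² = 84.9, so 85 per arm. Adjusting for baseline multiplies this by 1 − ρ², where ρ is the pre-post correlation:

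- ρ = 0.3: 84.9 × 0.91, so 78 per arm
- ρ = 0.5: 84.9 × 0.75, so 64 per arm
- ρ = 0.7: 84.9 × 0.51, so 44 per arm

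A simple change score multiplies it by 2(1 − ρ), giving 119, 85 and 51. Adjustment therefore needs fewer people than either alternative at each of these correlations.

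**The case against.** The strongest reply is that the trial already has a sound comparative test. The Statistical analysis section tests control against experimental, and the abstract applies the comparison at every visit, so month 12 is included. Under randomisation that test is valid, and the simulation confirms its error rate. Reporting before-after tests beside it does not alter that rate, and no passage says that within-arm significance will be used to claim benefit. All of this stands. A reader might infer that the program is never tested against control, or that the maintenance objective has no valid test at all. The documents support neither inference: a between-arm difference at 9 or 12 months is a reasonable, if partial, reading of maintenance.

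Two other inferences also fail.

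- The ANOVA might be thought to treat five correlated visits as independent groups. It is labelled within-subject, and a one-factor within-subject ANOVA is ordinarily a repeated-measures analysis.
- It might be tempting to quote the chance that exactly one arm is significant, 2p(1 − p), or about 25% to 49%. Half of that is the opposite pattern, which would not suggest benefit.

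It is also fair to say that testing separately within each arm is the natural reading of the before-after analysis but is not written down. Model form and a specific maintenance contrast could be left to an analysis plan that is not shown. Their absence alone would not be a finding. What an unseen plan does not cure is that this document states two different within-subject methods.

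**Conclusion.** The point holds in a limited form and should be fixed, but it does not leave the trial without a valid analysis.

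- The two within-subject statements conflict and must be reconciled. This rests on the text alone.
- Neither within-subject method can answer the comparative hypothesis. Read arm by arm, before-after tests would give the misleading pattern in about 13% to 25% of trials with no difference between arms. This assumes 85 completers per arm and an equal true change of 0.10 to 0.25 SD of change. The rate is lower outside that range, and it measures a risk of misreading, not the error rate of the planned between-arm test.
- The between-arm test is valid at each visit. As stated it makes no use of baseline, does not compare change between arms and does not isolate whether the between-arm effect is kept from month 6 to month 12.

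**What to change.** Replace the two within-subject statements and the unadjusted visit-by-visit tests, in both the abstract and the Statistical analysis section, with one mixed model for repeated measures. It should include baseline value, visit, group and group-by-visit, with correlation within subject. From it:

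- base the conclusion on the between-arm difference at 6 months;
- for maintenance, report the between-arm difference at 12 months and the between-arm difference in 6-to-12-month change, each with a confidence interval, and do not read a non-significant change as proof of maintenance;
- give within-arm changes descriptively, without p-values.

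The cost is revised wording, slightly more analysis work and reliance on the model's assumptions about distribution and missing data. All the data are already scheduled for collection. On the assumed difference of 0.43, the baseline-adjusted 6-month comparison fits within the planned numbers at each correlation shown.

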### Difficulties and limitations of the study

The main difficulty of the study is the possibility that the development of the workout sessions could be performed by a clinical physiotherapist specialized in therapeutic training with an ad hoc contract. As an alternative, the researchers themselves would have to acquire the necessary competences to carry out the workout sessions in coordination with the reference Rehabilitation Team (Fisiotherapy Unit – Clinical Management Unit of “Huelin”, Health District of Málaga).

## Discussion

If the hypothesis is accepted, it should achieve further improvements of the neuromuscular and physiological state in the elderly identified as frail, front the standard medical practice. The interaction of various intervention strategies, wherein a supervised workout program, medication review, diet adjustment and health education are included, will achieve further improvements in the elderly identified as frail. This protocol, if beneficial, could be implemented within public health, after certain requirements are resolved with regard to workout program, medication review, diet adjustment and health education, in order to improve the quality if life and the overall health in frail older adults.

### Trial status

This study is open for participant recruitment at the time of submission (enrolling by invitation as of day 1/1/2019).

## Data Availability

Not applicable as this is a study protocol with no gathered data.

## Abbreviations

BMI: Body Mass Index
CONSORT: Consolidated Standards of Reporting Trials
IRHR: Intensity Relative to the Heart Rate
RM: Maximum Repetitions
SPPB: Short Physical Perfomance Battery
